### 3.4.2 Design

For the second cost-effectiveness analysis, an alternative measure of effectiveness will be years of life saved. Population-level data is the only valid way to directly measure the effect of the intervention on health outcomes.

It is expected that the capacity-building and quality improvement interventions will reduce mortality by improving the emergency triage and treatment of patients and improving the quality of care for infectious diseases. The Uganda Child Verbal Autopsy Study showed that 75% of children who died received care from a government or private hospital or health center.[[35]](#endnote-36) Given that these children had access to care, it may be possible to save their lives by improving the quality of that care.

When the quality of care improves, utilization of a health facility increases.[[36]](#endnote-37) [[37]](#endnote-38) If the quality of care improves at the Phase 1 sites, they are likely to attract more patients including sicker patients. Paradoxically, as the quality improves the mortality of patients at the facility may increase, because the volume of patients and case complexity increases. Population-level data at the Phase 1 sites would reveal that population-level mortality had decreased because more people are seeking care, even if facility-level mortality increased.

UBOS proposed estimating population-level mortality with a two-part sampling method that builds on recent advances in the Demographic Surveillance Systems in which representatives of local council members at the parish level provide information about recent deaths. Although vital records systems may not be reliable in many African countries, there is a policy in Uganda for citizens to report births and deaths to the local council members. The information is more reliable in rural parishes than urban.

In the first part, the local council member directs the interviewers to households where there is a “high index of suspicion” that a death of a child U5 has occurred. To ensure completeness, a listing of households in each enumeration area (EA) would be created from interviews with all households in collaboration with the local council member. The listing includes an identification number and location for each household, whether or not a death occurred within the household in the last 3 years, and if yes, the age of the person at the time of his/her death.

Households will be selected from 2 strata/tiers for household and birth history interviews.

1. 100% of all households that report a child who was less than five years at the time of his/her death died in the last three years. We expect an average of 4.2 deaths per EA (.028 mortality rate * 150 households/EA * 1 child/household) per year, or 12.6 in 3 years.  Some EA will have more households in the numerator and some will have less.
2. A random sample of 30 households. (See section 3.4.4 below). On average 2.5 household with a death will be among the 30 households selected at random to calculate the denominator.  (30 household in sample/150 household in EA = 0.2 probability of selected at random.  12.6 households in numerator * 0.2=2.5 households.)    We would have their information from strata/tier 1, and they would not need to be re-interviewed in stata/tier 2. On average, this would bring the number of new interviews for strata/tier 2 down to 28 instead of 30. Some EA will have more new interviews for strata/tier 2 and some will have less. Conservatively, we should continue to plan on conducting interviews with 30 household in strata/tier 2.

The IDCAP mortality survey differs from DHS, because we are interested in exposure to the IDCAP intervention, i.e. the length of time that people live within 5 km of the IDCAP site. The following information is needed on each member of the household: a)birth date (age), b) link to “natural” mother, i.e. is birth mother included in household listing**,** c)exposure, i.e. number of months living in household or EA **,** d) Vital status i.e. alive or dead, e) if death, date of death and residence on date of death.

### 3.4.3 Setting

The mortality data will be collected from households that live within five kilometres of the IDCAP sites. See Section 3.1.3 for a list of the site selection criteria.

### 3.4.4 Population

Sample sizecalculations were based on child mortality results from the evaluation of the Integrated Management of Child Illness (IMCI) in Tanzania.[[38]](#endnote-39) During the two years after IMCI was initiated, the mortality rate in the IMCI districts was 24.4 per 1000 person years compared to 28.2 in the comparison districts, i.e. 13% lower. A similar 13% decrease in mortality was associated with IMCI in Bangladesh.[[39]](#endnote-40)

[name], PhD, Professor of Biostatistics at the University of Washington derived the equations to calculate the power and sample size for a sampling procedure designed with the following 4 features:

- All U5 deaths in an EA during the period of interest are identified
- The total number of households in the EA is known
- A random sample of c households is taken in the EA
- The number of children U5 in the random sample is determined (this sample may, by chance, include households with a death, but, in general, this sample of c households will be *in addition* to the HHs in which there has been a death)

The sample size and power calculations are based on the following four assumptions.

- 150 households per EA
- On average 1 child U5 per household
- U5 mortality per year at baseline : .028
- 13% reduction in this mortality rate

The number of people per household in the 2006 Uganda Demographic and Health Survey (DHS) was five.[[40]](#endnote-41) The percentage of children under five years was 19.2% or approximately one child under five years per household. This is comparable to the Iganga/Mayuge demographic surveillance site in which a sample of 12,000 households provided data on 64,000 individuals or 5.3 people per household. The sample included 12500 (19.5%) children under five years

For 80% power to detect a 13% reduction from a baseline mortality rate of .028 one would need (ignoring clustering):

| **c+** | **#EAs per arm** | **Estimated number of U5 children sampled per arm** |
| --- | --- | --- |
| 10 | 283 | 3942 |
| 15 | 256 | 4846 |
| 20 | 242 | 5790 |
| 30 | 229 | 7770 |

+ Number of HHs sampled in an EA to estimate denominator

* This is U5 children sampled for the denominator + deaths

If we include the effect of clustering,[[41]](#endnote-42) with known denominator and assuming 150 households per EA and sampling of 30 households per EA, the sample size requirements increase to about 260 EAs per arm for a mortality rate coefficient of variation =.25 and to 310 per arm for coefficient of variation=.35.

With a sample of 300 EAs per arm, the household listing would collect mortality data from 45,000 household per arm, and household and birth history data from 12,600 household per arm. Assuming equal sample sizes in each arm, about 35000 children per arm would be required to detect a 14.6 difference. These initial calculations would have to be refined to adjust for the interclass correlation (ICC) associated with sampling several children from the same household.

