### 3.3.4 Population

For the purpose of the sample size calculation, the unit of analysis is the site. Calculations of the number of sites required and statistical power focused on two malaria indicators and site-level data from eight Joint Uganda Malaria Training Program sites 120 days before training and 120 days after training. The mean change and standard deviation among the eight sites are in columns 1 and 2 of Table 4. The proposed evaluation is designed to detect an 18- point (20-point) difference between the treatment and the control group. Calculations of the number of sites required were based on a power of 80% and alpha of .05 using the sample size program in Stata version 10. Table 3 shows four calculations using two indicators for two different age groups. Column 3 indicates that 18 sites are required per treatment group to achieve 80% power for the first indicator for patients 5 years or more, but that the proposed design of 16 per group will be adequate for the others. Similarly, column 4 indicates that the proposed design will have only a 76% chance of detecting a difference of 10 points for the first indicator for patients 5 years or more, but that that there is a high probability (81% to 100%) of detecting differences for the other indicators. It is likely that the proposed design will provide sufficient power for other indicators as well. If site-level covariates are added to the site-level regression analysis, the power may be higher than shown here.

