# 3.4 Mortality Survey

### 3.4.1 Methods

The second method of the cost-effectiveness analysis will be a compare the incremental cost estimates described above with mortality data. IDCAP has contracted with the Uganda Bureau of Statistics (UBOS) to measure the impact of the IDCAP intervention on mortality rate among children under five (U5) who live within the 5km radius of each of the 36 health facilities where IDCAP is operating countrywide. The mortality rate is the ratio of the number of deaths among children U5 to the total number of children U5 during a 12 month period. The impact will be measured as the “difference in differences,” i.e. the difference in the mortality rate at 18 phase 1 sites (intervention) compared to the difference at 18 phase 2 sites (control), where the difference in the mortality rate is the average baseline mortality rate minus the mortality rate during Phase 1. A comparison of the difference in mortality in phase 1 sites to phase 2 sites will provide an alternative estimate of the incremental benefit (i.e. B3 of Table 2). The incremental cost effectiveness ratio will be estimated as the ratio of the incremental cost (i.e. B4 of Table 2) to the difference-in-difference in mortality between phase 1 and phase 2 sites.

A 3-year recall period is set for this survey i.e. from April 2008 to the present, including 1.5 or 2 years of baseline data (April 2008-March 2010), and 12 or 18 months of data after the intervention began (April 2010 to September 2011).

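### The mortality survey is sized for a two-arm comparison of one 12-month rate, but the planned analysis is a difference in differences, whose baseline variance the power calculation leaves out

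*Protocol*

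**What the plan says.** Section 3.4.1 defines the mortality effect as "the difference in the mortality rate at 18 phase 1 sites (intervention) compared to the difference at 18 phase 2 sites (control"), each difference being "the average baseline mortality rate minus the mortality rate during Phase 1". It gives a baseline of 1.5 or 2 years and 12 or 18 months of data after the intervention began.

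Section 3.4.4 sizes the survey from four assumptions: 150 households per EA, one child under five per household, "U5 mortality per year at baseline : .028", and a "13% reduction in this mortality rate". Its table is headed "For 80% power to detect a 13% reduction from a baseline mortality rate of .028 one would need (ignoring clustering") and gives 283, 256, 242 and 229 EAs per arm when 10, 15, 20 or 30 households per EA are sampled for the denominator.

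Once clustering is allowed for, the section reports that "the sample size requirements increase to about 260 EAs per arm for a mortality rate coefficient of variation =.25". At a coefficient of variation of .35 the figure is 310. Both are obtained "with known denominator and assuming 150 households per EA and sampling of 30 households per EA". The section then works out household numbers for 300 EAs per arm.

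**The concern.** A difference in differences subtracts an estimated baseline rate in each arm, so the sampling error of both baseline rates enters the variance. None of the four sizing assumptions concerns a baseline period. If the calculation covers only one period, its 80% does not describe the analysis in 3.4.1.

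This contrast is the denominator of the second cost-effectiveness ratio and half of the comparison in specific objective 4. If power is overstated, a null mortality result would be read as stronger evidence of no effect than it is.

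**Working it through.** **Inputs.** From 3.4.4: p0 = .028 per year; p1 = .87 × .028 = .02436; difference .00364; 150 households per EA with one child each; c sampled households; 80% power. Section 3.4.4 gives no alpha. I take .05 from 3.3.4 ("based on a power of 80% and alpha of .05 using the sample size program in Stata version 10") and assume it is two-sided; one-sided would give 180 EAs at c = 30, not 229. The multiplier is (1.960 + .842)² = 7.849.

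**1. The printed table.** For one 12-month period and two arms:

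EAs per arm = 7.849 × [(p0 + p1)/150 + (p0² + p1²)(1/c − 1/150)] / .00364²

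At c = 30 the bracket is .00034907 + .00003673 = .00038580, and 7.849 × .00038580 / .0000132496 = 228.5. For c = 10, 15, 20 and 30 the results are 282.9, 255.7, 242.1 and 228.5, against 283, 256, 242 and 229 printed. The children column agrees: one year of deaths per EA is 150 × (.028 + .02436)/2 = 3.93, and 229 × (30 + 3.93) = 7,769, against 7,770. There is no baseline term.

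**2. The clustered figures.** With coefficient of variation k and a known denominator:

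EAs per arm = 1 + 7.849 × [(p0 + p1)/150 + k²(p0² + p1²)] / .00364²

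This gives 258.8 (k = .25) and 307.7 (k = .35), against about 260 and 310. Again there is no baseline term. Adding the table's own denominator term, (p0² + p1²)(1/30 − 1/150), gives 280.5 and 329.5.

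**3. The difference in differences.** Let B and F be the baseline and follow-up lengths in years, with the control rate steady at .028 and no clustering. If the same 30 households supply both denominators, so that their error nearly cancels, the variance per EA is

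V = (p0 + p1)/(150F) + 2p0/(150B) + (1/30 − 1/150)(p0 − p1)²

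If the two periods' denominators are independent, the last term becomes (1/30 − 1/150)(3p0² + p1²). With n EAs per arm, power = Φ(.00364/√(V/n) − 1.96).

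Example, B = 2, F = 1, n = 229: V = .00034907 + .00018667 + .00000035 = .00053609; √(V/229) = .001530; .00364/.001530 = 2.379; power = Φ(.419) = 66.2%.

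In each cell below, the two values are for an 18-month and a 24-month baseline.

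| Follow-up | 229 EAs, shared denominator | 229 EAs, independent denominators | 300 EAs, shared denominator |
| --- | --- | --- | --- |
| 9 months | 54.0%, 57.8% | 49.9%, 53.1% | 65.5%, 69.4% |
| 12 months | 61.5%, 66.2% | 56.3%, 60.4% | 73.2%, 77.7% |
| 18 months | 70.9%, 76.7% | 64.3%, 69.4% | 81.9%, 86.8% |

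For 80% power with shared denominators and no clustering, the requirement is 354 and 318 EAs at 12 months, and 286 and 249 at 18 months, against 229 printed.

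**4. Clustering.** If EA-level deviations persist fully between periods, they almost cancel and the table barely changes. With between-period correlation ρ the added variance per EA is k²[p0² + p1² − 2ρp0p1 + 2p0²(1 − ρ)]. At k = .25 and ρ = .5, 300 EAs with shared denominators give about 60-64% (nine months), 67-71% (12 months) and 75-80% (18 months). The protocol gives no value for ρ; .5 is my assumption.

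**The case against.** The strongest reply is that 229 is the row that ignores clustering, and 3.4.4 goes on to 260-310 and then works with 300 per arm. With no clustering or fully persistent EA effects, shared denominators and 18-month follow-up, 300 EAs exceed 80%. This stands: it is not shown that the survey at 300 EAs falls short under every stated window. But the increase was made for clustering, not for baseline error, and it falls short for 12-month follow-up.

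Section 3.4.4 also calls its calculations initial and in need of refinement. The only refinement it names is for several children in one household. It states openly that the clustered figures take the denominator as known, so that is a disclosed simplification, though the sampling plan does not support it. Section 3.0 says no final decision on collecting mortality data had been made, although 3.4.1 reports a contract for the survey.

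Two stronger readings are tempting. A reader might put power as low as 53%, but at 229 EAs that needs a 12-month baseline under shared denominators, and the protocol plans 1.5 or 2 years. A reader might also say the protocol claims 80% power for a difference in differences. It does not: 3.4.4 claims 80% for a 13% reduction without naming the analysis. The defect is the mismatch with 3.4.1.

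**Conclusion.** The point holds. The sizes in 3.4.4 are for one 12-month rate in two arms and leave out the variance of the baseline rates that 3.4.1 subtracts. At 229 EAs per arm, difference-in-differences power is below 80% under every stated window: about 62-77% with shared denominators and 56-69% with independent ones. At 300 EAs it is about 73-87% over the stated windows, without clustering and with shared denominators, so it may fall on either side of 80%.

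The nine-month figures (54-58% at 229 EAs, 65-69% at 300, shared denominators) apply if the follow-up rate is confined to a nine-month Phase 1. Section 2.3 has Phase 2 sites starting on-site support nine months later, whereas 3.4.6 puts Phase 1 support at 18 months in total. These passages must be reconciled before any power figure can be final.

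The results rest on a two-sided alpha of .05, a steady control rate, a full 13% effect throughout follow-up, and the stated denominator assumptions. The protocol does not say how each period's denominator is formed.

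**What to change.** In 3.4.4, recompute power, or the detectable reduction, for the analysis actually used. Fix one baseline window and one follow-up window, include the baseline variance, say how each period's denominator is obtained, and keep the sampled-denominator term in the clustered figures. On the single-period formula that term alone moves about 260 and 310 to about 281 and 330. Reconcile the length of Phase 1 between 2.3 and 3.4.6 at the same time.

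Optionally, in 3.4.1, replace the difference in differences with a site-level regression of the follow-up mortality rate on arm and the site's baseline rate, the form 3.3.2 already uses for the performance indicators. It is generally at least as precise, apart from the small cost of estimating the slope with 36 sites. That advantage is a large-sample property, and restating power resolves the mismatch without it.

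The cost is wording and a recalculation. Baseline data are already to be collected. The stated power may be less favourable.

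### The clustered mortality sample sizes (about 260 and 310 EAs per arm) treat the child denominator as known, although the survey estimates it from 30 of 150 households; restoring that error adds about 22 EAs per arm

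*Protocol*

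**What the plan says.** Section 3.4.4 describes a two-part survey. All under-five deaths in an EA are identified and the total number of households is known. The number of children is obtained by sampling: "A random sample of c households is taken in the EA", and children are counted only in those households. The table's footnote describes c as the sample used to estimate the denominator. Section 3.4.2 fixes c at 30 and gives it the same purpose.

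The planning assumptions are "150 households per EA", "On average 1 child U5 per household" and "U5 mortality per year at baseline : .028". The table that ignores clustering is headed by "For 80% power to detect a 13% reduction from a baseline mortality rate of .028" and gives 283, 256, 242 and 229 EAs per arm for c = 10, 15, 20 and 30.

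The next paragraph adds clustering, "with known denominator and assuming 150 households per EA and sampling of 30 households per EA", and reports about 260 EAs per arm at CV .25 and 310 at CV .35. It then describes the volume of data: "With a sample of 300 EAs per arm, the household listing would collect mortality data from 45,000 household per arm". The only further refinement it names is for correlation between children of the same household.

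**The concern.** A known denominator and a denominator estimated from one fifth of the households are different designs. The household listing in section 3.4.2 does not bridge the gap: it records each household's identifier and location, any death in the last three years and the age at death, but not the number of living children under five.

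The table falls from 283 to 229 as c grows, so it carries a penalty for estimating the denominator. If the clustered figures drop that penalty, they start from a lower base than the 229 printed just above them. A reader comparing 229 with 260 or 310 would then understate the cost of clustering, and the stated 80% power would not hold for the design described. The survey supplies the mortality-based measure of effectiveness for specific objective 4.

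**Working it through.** **Inputs.** From section 3.4.4: r0 = .028; a 13% reduction, so r1 = .028 × .87 = .02436; 150 households with one child each, so 150 child-years per EA in one year; 80% power; equal arms; k = .25 or .35. Section 3.4.4 states neither alpha nor sidedness. I take .05 from the facility calculation in section 3.3.4 ("based on a power of 80% and alpha of .05"), two-sided. One-sided alpha does not reproduce the figures; it gives 180 rather than 229 at c = 30.

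**Common quantities.**
- (1.96 + .8416)² = 7.849
- (r0 − r1)² = .00364² = 1.325 × 10⁻⁵
- F = 7.849 / (1.325 × 10⁻⁵) ≈ 592,400
- S = r0² + r1² = .0013774, so F × S ≈ 816

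**Step 1: the unclustered table.** With a known denominator, EAs per arm = F × (r0 + r1)/150 = 206.8, whatever c is. Estimating the denominator from c of 150 households adds F × S × (1/c − 1/150). This treats children per household as Poisson with mean 1 and applies a finite-population correction.

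| c | Added term | Total | Stated |
|---|---|---|---|
| 10 | 76.2 | 282.9 | 283 |
| 15 | 49.0 | 255.7 | 256 |
| 20 | 35.4 | 242.1 | 242 |
| 30 | 21.8 | 228.5 | 229 |

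All four rows match to the unit, so the table includes the term.

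**Step 2: the clustered figures.** The cluster-rate formula with a known denominator is 1 + F × [(r0 + r1)/150 + k² × S].
- k = .25: 1 + 206.8 + 51.0 = 258.8 (stated about 260)
- k = .35: 1 + 206.8 + 100.0 = 307.7 (stated 310; components rounded)

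Both agree with the stated figures, so these were built on 206.8 rather than 228.5.

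**Step 3: restore the c = 30 term.**
- k = .25: 258.8 + 21.8 = 280.5, about 281
- k = .35: 307.7 + 21.8 = 329.5, about 330

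**Step 4: power.** Power = Φ(√[(n − 1)(r0 − r1)²/V] − 1.96), where V = (r0 + r1)/150 + k² × S, plus S × (1/30 − 1/150) when the denominator is estimated.

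| EAs per arm | CV | Known denominator | Estimated from 30 |
|---|---|---|---|
| 260 | .25 | 80.2% | 76.9% |
| 310 | .35 | 80.3% | 77.6% |
| 300 | .25 | 85.5% | 82.6% |
| 300 | .35 | 79.0% | 76.2% |

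**Sensitivity of the corrected sizes.**
- Taking r1 as .0244 (the cited Tanzanian rate) gives 287 and 337.
- Dropping the finite-population correction gives 286 and 335, but then c = 30 gives 234 in the table rather than 229.
- A variance of children per household between 0.5 and 1.5 scales the 21.8 to between 10.9 and 32.6, giving 270 to 291 and 319 to 340.

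**The case against.** **The assumption is disclosed.** The known denominator is named in the same sentence as the results, the first figure is given as approximate, and the calculations are called initial. That is fair: this is a labelled simplification, not a hidden slip. But the label describes a survey other than the one planned, and the refinement the text promises concerns a different source of error.

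**The effect is small.** The omitted term is about 22 EAs, against 50 between the two CV scenarios. That stands, and it limits the weight of the point. The survey also serves the alternative cost-effectiveness measure, not the primary facility comparison in section 3.3.2.

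**The formula is inferred.** Section 3.4.4 says equations were derived but does not print them, and it only cites the clustering method. Alpha, sidedness, Poisson household counts and the finite-population correction are therefore inferences, supported by the match to six stated figures.

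**The calculation is not the survey's planned analysis.** It is a one-year comparison of two groups of EAs. Section 3.4.1 plans 12 or 18 months of follow-up and a difference in differences against baseline, and sites rather than EAs are randomised. With 18 months (225 child-years per EA) and the denominator term kept, the same formula needs about 212 and 261 EAs, and 300 gives 92% and 85% power. Baseline differencing would change this again, in a direction the document does not settle. So 281 and 330 correct the stated calculation; they are not the survey's actual requirement.

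**Two stronger readings are tempting.** A reader might infer that 300 EAs contradicts the protocol's own 310. It does not: 300 lies between the two scenarios, introduces a description of data volume, and is never said to cover CV .35. A reader might also infer that the survey is underpowered at the last size quoted. On this basis that is so only at CV .35; at CV .25, 300 EAs still gives about 83%.

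**Conclusion.** The point holds as an inconsistency in a stated figure. Section 3.4.4 estimates the child denominator by sampling and allows for this in the unclustered table, then omits it when adding clustering. On the reconstructed formula the clustered requirement is low by about 22 EAs per arm (7 to 8%), and power at the two stated sizes is 2 to 3 points below 80%.

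This rests on two-sided alpha .05, Poisson children per household with a finite-population correction, one year of exposure and the EA as the cluster. It does not depend on whether the site should be the cluster, which is a separate matter. It does not show that the survey as a whole lacks power.

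**What to change.** In section 3.4.4, remove the statement that the denominator is known. Then do one of the following:
- restate the clustered requirement as about 281 EAs per arm (CV .25) and 330 (CV .35); or
- keep the printed sizes and restate their power: about 77% at 260 (CV .25), 78% at 310 (CV .35), and 83% and 76% at 300 (CV .25 and .35).

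Either way, state the assumptions (alpha and sidedness, the distribution of children per household, the finite-population correction) for the authors to confirm against their own equations. Add that the figures are on a one-year, EA-level basis and exclude site-level clustering and baseline differencing. Any later revision of the clustering calculation should keep the denominator term.

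The cost is a change of wording and a slightly less favourable stated figure. No additional EAs or fieldwork are requested.

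### The mortality sample size counts enumeration areas as independent clusters and omits clustering by randomised site, so the stated 80% power is not shown for a design with 18 sites per arm.

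*Protocol*

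**What the plan says.** Protocol section 3.4.1 defines the mortality effect as a difference in differences: "the difference in the mortality rate at 18 phase 1 sites (intervention) compared to the difference at 18 phase 2 sites (control"). The Abstract and section 2.3 randomise sites, 18 to each phase, and make the site the unit of analysis for the comparison of phases. Section 3.4.3 draws households from within five kilometres of a site.

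Section 3.4.4 sets the sample size. It opens with a table headed "For 80% power to detect a 13% reduction from a baseline mortality rate of .028 one would need (ignoring clustering"), giving 283, 256, 242 and 229 EAs per arm when 10, 15, 20 or 30 households per EA are sampled for the denominator. The inputs are "U5 mortality per year at baseline : .028", a "13% reduction in this mortality rate", "150 households per EA" and "On average 1 child U5 per household". It then adds clustering, citing a paper on sample size for cluster-randomised trials: "the sample size requirements increase to about 260 EAs per arm for a mortality rate coefficient of variation =.25", rising to 310 at a CV of .35, with the denominator taken as known. It goes on to describe a survey of 300 EAs per arm. The only further refinement it promises is for several children from the same household.

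**The concern.** The allowance for clustering has to be made at the level at which treatment is assigned. Here that is the site: all EAs around one facility receive on-site support together or wait together. The calculation is expressed wholly in EAs, and the number 18 does not appear in it. If mortality differs between sites beyond chance, or moves differently over time from site to site, 300 EAs in 18 groups carry less information than 300 independent EAs.

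Mortality is the effectiveness measure in the second cost-effectiveness method, and so underlies objective 4 and hypothesis 4. If the true power is well below 80%, a null mortality result could be read as evidence of no effect, and the ratio built on it could be uninterpretable.

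**Working it through.** **Inputs.** Baseline rate l0 = .028; 13% reduction, so l1 = .028 × .87 = .02436 and D = .00364; 150 child-years per EA per year; 80% power (all section 3.4.4). Two-sided alpha of .05 is not stated for the survey. It is assumed from section 3.3.4, where the facility calculation is "based on a power of 80% and alpha of .05 using the sample size program in Stata version 10", and it reproduces the survey's figures. (1.96 + 0.842)² = 7.849; D² = .00001325; l0 + l1 = .05236; l0² + l1² = .0013774.

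**1. The no-clustering table.** EAs per arm = 7.849 × [(l0 + l1)/150 + (l0² + l1²)(1 − c/150)/c] / D², where c is the number of households sampled and (1 − c/150) is the finite-population correction. This gives 282.9, 255.7, 242.1 and 228.5, against 283, 256, 242 and 229.

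**2. The clustered figures.** The standard cluster-rate formula is: clusters per arm = 1 + 7.849 × [(l0 + l1)/y + k²(l0² + l1²)] / D². With y = 150, so that the cluster is one EA:
- k = .25: [.00034907 + .00008609] gives 258.8 (stated: about 260)
- k = .35: [.00034907 + .00016873] gives 307.7 (stated: 310)

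On that basis 300 EAs per arm give 85% and 79% power.

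**3. The same formula with the site as cluster, one period.** 300 × 150 / 18 = 2,500 child-years per site. Power = Phi(√(17 D² / [.00002094 + k² × .0013774]) − 1.96), and 17 D² = .00022524.

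| Between-site CV | Power |
| --- | --- |
| .35 | 19% |
| .25 | 31% |
| .15 | 55% |
| .10 | 72% |
| about .075 | 80% |

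For k = .25: √(.00022524/.00010703) = 1.451, and Phi(1.451 − 1.96) = .305.

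**4. If the stated CVs are purely between EAs within sites.** Each site averages 300/18 = 16.7 EAs, so the site-level CV is .25/√16.7 = .061 or .35/√16.7 = .086. Power is 84% or 77%. Intermediate splits lie between: with a quarter of the squared CV between sites, 60% or 43%; with half, 45% or 30%.

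**5. The planned difference-in-differences.** Section 3.4.1 allows up to two years of baseline (5,000 child-years per site) and 12 or 18 months after the start (2,500 or 3,750). Stable site differences cancel. Let s be the CV of site-by-period variation in each period. The bracket becomes (l0 + l1)/y1 + 2·l0/5000 + s²(l0² + l1² + 2·l0²), and the last sum is .0029454.
- s = 0: .00003214 at 12 months, 75%; .00002516 at 18 months, 85%
- s = .10: .00006160 at 12 months, 48%; .00005462 at 18 months, 53%

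**6. Denominator sampling.** Adding (l0² + l1²) × .8/30 to the bracket in step 2 (30 households, same finite-population correction) gives about 281 and 329 EAs per arm, still with the EA as cluster.

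**The case against.** The strongest reply is that power of 19% to 31% is not established. A reader might infer that range by moving the stated CVs of .25 and .35 to site level. The protocol uses them in an EA-level calculation and never says at which level they apply, so that step is itself an assumption; step 4 shows the opposite assumption giving 84% or 77%. That range also belongs to a one-period comparison, whereas section 3.4.1 plans a difference-in-differences in which stable site differences drop out. This stands. It is not possible to say that 80% power is absent, only that it has not been shown.

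A reader might also infer that the analysis will use standard errors at EA or child level that are too small. Nothing in the protocol proposes this, and the Abstract already names the site as the unit for hypotheses 2 to 4. The planned difference-in-differences need not be replaced by another model.

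The known denominator is a declared simplification, and step 6 shows that its effect is moderate. Section 3.4.4 calls its figures initial, and section 3.0 says that the decision to collect mortality data is not final (section 3.4.1 nevertheless reports a contract for the survey). These points lower the urgency. They do not answer the main one, because the only refinement promised concerns children in the same household and would not bring in the site.

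**Conclusion.** The statement is wrong as written and should be fixed. Figures presented as allowing for clustering do so at EA level only, while treatment is assigned to 18 sites per arm. The arithmetic reproduces; the error is in the level of the cluster.

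The size of the loss cannot be fixed from the protocol. It depends on the between-site CV for a one-period comparison, and on site-by-period variation (equivalently, the before/after correlation) for the planned analysis. Neither is given. Under the planned analysis, 80% is reached only when site-by-period variation is small and follow-up runs to 18 months. Even with none, 12 months gives about 75%. All results in steps 3 to 5 assume two-sided alpha of .05, 300 EAs spread equally over 18 sites, a known denominator and a full 13% effect throughout follow-up. Under the nine-month stagger in section 2.3, later follow-up includes time when Phase 2 sites also receive support, so the 18-month figures are, if anything, favourable.

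**What to change.** In section 3.4.4, replace the 260/310-EA statement and its 80% power with power and detectable reduction for 18 randomised sites per arm under the difference-in-differences of section 3.4.1. Show them over a range of between-site and site-by-period CVs, and state the level of each CV, the baseline and follow-up lengths, alpha, and whether the denominator is known or sampled. If an EA-based figure is kept for planning fieldwork, give it with denominator sampling included (about 281 and 329).

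Confirm in section 3.4 that the site is the unit for the mortality analysis, in line with the Abstract. If the restated power is inadequate, describe the mortality-based cost-effectiveness result as exploratory.

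The cost is wording only: no change to sites, randomisation or data collection. The stated power becomes less favourable.
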